#### Withdrawal Criteria

Subjects will be withdrawn from this study at the discretion of the researchers if there are safety concerns or if the children are unable to complete follow-up examinations.

#### Sample Size

There are no directly available data to assess the relationship between connectome-based features and clinical assessments of children with BCP to predict their communication ability at school entry. The sample size was calculated according to a previous study (Coleman et al., 2016). In that study of children with CP with a total sample size of *n* = 131, the number of children with communication abnormalities was 62 (47.0%). Multiple linear regression showed that lesion type and five semiquantitative indices that reflected the severity of brain lesions were related to the communication assessment score. However, the efficient size f2 cannot be directly calculated because the R2 and residual variance in the multiple regression model were not reported in the study (Coleman et al., 2016). Geytenbeek et al. (2015) used multiple linear regression based on MRI measures to evaluate language comprehension in non-speaking children with severe CP and PWMLs; that study revealed that the R2 of the model was 0.36. Choi et al. (2017) also found significant negative relationships between the severity of PWMLs and expressive language and between the severity of PWMLs and receiving language performance. Although the above results indicate that the MRI measures could be used to adequately predict communication performance in children with CP, we still assumed a lower efficient size for the MRI measures (f2 as 0.10) to ensure a sufficient sample size for an accurate prediction of communication performance in children with CP. Based on previous studies (Geytenbeek et al., 2015; Coleman et al., 2016; Choi et al., 2017), the number of predictors was set as 6. If α = 0.05, 1-β = 0.80, then the study requires enrollment of 143 participants according to the power calculation by G*Power, version 3.1.9 (Faul et al., 2009). According to previous follow-up experience and given a maximum anticipated dropout rate of 20%, a total sample size of 178 children with BCP and PWMLs will be needed.

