#### Development and Validation of Prediction Models

According to previously reported literature, for children with CP, the distribution of their CFCS grades is unbalanced and skewed. None or mild communication impairment (CFCS level I, II, III) in children with CP and PWMLs is more common than in those with severe communication impairment (CFCS level IV, V) (Kristoffersson et al., 2020). Such an imbalance distribution will cause misprediction during the process of predictive model generation (Saethang et al., 2016). Thus, we defined individuals who communicate at CFCS level I (defined as “effective sender and receiver communication with unfamiliar and familiar partners”) as having an absence of communication impairment. Patients with CFCS level I will be classified into the absence of communication impairment group, and those with CFCS levels II, III, IV, and V will be classified into the communication impairment group. In this way, the CFCS grade will be converted to a binary indicator, and our study will focus on identifying whether children with BCP have any communication impairment and improving the efficacy of the predictive model. All the variables will be centered and standardized before being entered into each model, which will be created with machine learning algorithms. In machine learning, the no-free-lunch theorem states that there is no one model (or, more generically, machine learning tool) that will work best for every problem (Wolpert and Macready, 1997). Therefore, several classification algorithms with varying hyperparameters will be evaluated using support vector machine, random forest, logistic regression, and other methods to investigate which algorithm will outperform competing approaches across all settings. The workflow of data processing and communication prediction is outlined in Figure 2. The detailed model building and validation steps are as follows.

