Images from four sites (four hospitals) will be randomly partitioned into four equal portions. Approximately three-quarters of these images will be used as a “training cohort,” and the remaining one-quarter of these images will be used as a “test cohort.” In the “training cohort,” the proportion of lesioned voxels in the ROI and the links of the connectome matrix that are not shown difference between absence of communication impairment group and communication impairment group will be excluded, where the significance level is defined as *P* < 0.05 without multiple comparison correction in the two-sample test. The selected features will be used to define models predicting presence or absence of communication impairment in children with BCP. For each prediction model, 10-fold cross-validation (CV) will be used to evaluate the performance. This means that the “training cohort” will be divided into a training (nine folds) and a validation dataset (one fold), leaving 9 of 10 participants in the training dataset and the remaining participants in the testing dataset. For the training cohort, the various hyperparameters within each algorithm will be used to determine the prediction model. Then, the model will be applied to the validation dataset to predict children with the presence or absence of communication impairment (predicted label). The same procedure will be repeated with each of the one-fold participants or the left-out participants in the leave-one-out procedure, serving as the validation dataset for 10 iterations. Thus, each subject will receive a predicted label, and the accuracy of predictive model will be evaluate by comparing predicted labels to true labels of BCP children. The CV step will be repeated 100 times with random cohort designation to select the model with the best prediction accuracy. The whole “training cohort” will be reused in its entirety to retrain the model based on the classification algorithm and hyperparameters of the prior selected model. Then, the retrained model will be used to evaluate the “test cohort,” and the communication performance of every subject of the “test cohort” will be predicted by the model. The final accuracy of the prediction model will be defined by comparing predicted labels to true labels of BCP children in the “test cohort,” The Receiver Operating Characteristic (ROC) curve and the area under curve (AUC) will be calculated to evaluate the predictive ability of built models. A two-sided Hotelling-Williams test (Steiger, 1980) will be used to determine whether the multimodality prediction model is more accurate than any of the single-modality prediction models. *P* values < 0.05 will be considered indicative of statistically significant differences across models. Given the possible effects of age on imaging measures, the “test cohort” will be divided into three groups: younger (6–12 months), middle-aged (12–18 months), and elderly (18–24 months years), according to their age at MRI scan. The optimal model will be applied to all subgroups to exam whether the prediction accuracy changes with age at MRI scan.

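### The 80% power behind the 143 children belongs to a linear-regression F test on all completers; it does not apply to the planned classifiers, which are judged on about 36 to 45 children

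*Protocol article*

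**What the plan says.** The Sample Size section starts from earlier studies that related MRI measures to communication scores by regression: "Multiple linear regression showed that lesion type and five semiquantitative indices that reflected the severity of brain lesions were related" to the score in one of them. It then fixes the inputs: "we still assumed a lower efficient size for the MRI measures (f2 as 0.10", and "the number of predictors was set as 6". With alpha 0.05 and power 0.80, the result is "then the study requires enrollment of 143 participants according to the power calculation", and after a maximum dropout of 20%, "a total sample size of 178 children with BCP and PWMLs will be needed". The low effect size is presented as a safeguard that makes the sample large enough for accurate prediction.

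Preselection of Predictive Features says that the feature sets hold hundreds to thousands of features. Development and Validation of Prediction Models dichotomises the outcome at CFCS level I versus II to V: "In this way, the CFCS grade will be converted to a binary indicator". Support vector machines, random forests, logistic regression and other classifiers are then built after univariate screening at P < 0.05. On the split it says: "Approximately three-quarters of these images will be used as a" training cohort. The remaining quarter is the test cohort, which supplies the final accuracy and the ROC curve. Models are compared by a two-sided Hotelling-Williams test at P < 0.05, and the test cohort is divided again into three age groups.

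**The concern.** The sample-size rationale and the analysis answer different questions. The first asks whether six fixed predictors explain any variance in a continuous score, using every completer. The second asks how well a classifier chosen from many candidates labels individual children it has not seen, using a quarter of them. The Sample Size section mentions neither the binary outcome, nor the split, nor the comparison between models.

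A reader of the section would take the primary aim, an individual prediction model, to be supported at 80% power. What that aim depends on is the precision of accuracy and AUC in the test cohort and the ability to separate the lesion, connectome and combined models there. The rationale gives neither.

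**Working it through.** **1. The plan's own figure.** Inputs from Sample Size: f2 = 0.10, 6 predictors, alpha 0.05, power 0.80. The section does not name the G*Power test, so it is inferred from these inputs and the match.

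- Overall F test of R2 = 0: df = (6, N − 7), noncentrality λ = f2 × N.
- N = 143: λ = 14.3, df = (6, 136), power 0.801.
- N = 142: λ = 14.2, power 0.798.
- The smallest N reaching 0.80 is therefore 143, as stated. A test of one coefficient among the six would need only 81, so that is not the test used.
- f2 = 0.10 corresponds to R2 = 0.10/1.10 = 0.091. Rejecting R2 = 0 at that effect size does not show accurate prediction for individual children.
- Dropout: 143/0.80 = 178.75, which rounds up to 179; the article has 178.

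**2. Numbers in the planned analysis.**

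| | Children with outcome | Training (3/4) | Test (1/4) |
|---|---|---|---|
| 20% dropout | 143 | 107.25 | 35.75 |
| No dropout | 178 | 133.5 | 44.5 |

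That is about 107 to 134 for training and 36 to 45 for testing. The three age groups would average 12 to 15 children each.

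**3. Precision of the test-cohort AUC.** The article gives no target AUC, so values of 0.70 to 0.85 are assumed. The impaired share is taken as 47% (the earlier cohort in Sample Size) or 78% (the top of the range in the Introduction). Both are assumptions for CFCS II to V in this population.

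Hanley-McNeil: SE² = [A(1 − A) + (n1 − 1)(Q1 − A²) + (n0 − 1)(Q2 − A²)] / (n1 n0), with Q1 = A/(2 − A), Q2 = 2A²/(1 + A), n1 impaired and n0 unimpaired.

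Example: A = 0.75, n1 = 17, n0 = 19 gives Q1 = 0.600, Q2 = 0.643, SE = 0.083 and half-width 1.96 × 0.083 = 0.163.

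95% half-widths:

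| Test n | Impaired/unimpaired | AUC 0.70 | 0.75 | 0.80 | 0.85 |
|---|---|---|---|---|---|
| 36 | 17/19 (47%) | 0.174 | 0.163 | 0.149 | 0.131 |
| 36 | 28/8 (78%) | 0.191 | 0.174 | 0.154 | 0.130 |
| 45 | 21/24 (47%) | 0.155 | 0.146 | 0.133 | 0.117 |
| 45 | 35/10 (78%) | 0.170 | 0.155 | 0.137 | 0.116 |

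At an intermediate 60% impaired, the smallest values are slightly lower: 0.124 at n = 36 and 0.111 at n = 45. For scale, 143 children would give 0.081 to 0.086 at AUC 0.75.

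**4. Comparison of two models.** Assumed AUCs 0.75 and 0.85, correlation r between the two AUC estimates, 47% impaired. SE of the difference = √(s1² + s2² − 2 r s1 s2); power = Φ(0.10/SE − 1.96).

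| Test n | s1, s2 | r = 0.3 | r = 0.5 | r = 0.7 |
|---|---|---|---|---|
| 36 | 0.083, 0.067 | 20% | 26% | 38% |
| 45 | 0.074, 0.060 | 24% | 31% | 46% |

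This is a normal approximation to a paired AUC difference. It is not the Hotelling-Williams test that the plan names.

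**The case against.** The strongest defence is that the section attaches 80% only to its own calculation. It says openly that no direct data exist for connectome features, and it nowhere claims 80% power for test-cohort AUC or for comparing models. That stands as far as it goes. What remains is that this is the only rationale for the study size and that it is said to secure accurate prediction, which a test of R2 = 0 does not do.

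Several stronger readings are tempting, and the documents do not support them:

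- **That 143 is miscalculated.** It is not; it reproduces exactly.
- **That 178 leaves the study short.** The upward rounding is 179, but power at 142 is 0.798 against 0.801 at 143. This is a rounding remark.
- **That the study's real power is the same F test at the split sizes** (0.647 at 107, 0.202 at 36). The plan never runs that test. The results also depend on a deliberately low f2: the R2 of 0.36 cited in the section gives f2 = 0.36/0.64 = 0.56 and power of about 0.88 at n = 36.
- **That the test cohort will be 36.** The 20% is a maximum dropout; with none it is about 45.
- **That the test cohort is uninformative.** At n = 36, AUC 0.75 and 47% impaired, the interval is 0.59 to 0.91. That is wide, but it excludes 0.50.

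The absence of a separate analysis plan does not answer the point. The article states both the rationale and the analysis, and the two do not match.

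**Conclusion.** The concern holds as a mismatch between the sizing basis and the planned evaluation. The 80% power is correct for an overall linear-regression F test on 143 completers, and it is not a property of the classifiers trained on about 107 to 134 children and judged on about 36 to 45.

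For the planned evaluation, the expected AUC half-width is about 0.13 to 0.19 at n = 36 and 0.12 to 0.17 at n = 45. A 0.10 difference in AUC would be detected with roughly 20 to 38% and 24 to 46% power. These sizes rest on assumed AUCs, impaired shares and correlations, and on approximations, because the article gives no targets. The mismatch itself rests on none of them; its one inference is which G*Power test was used, and the exact match at 143 supports it.

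**What to change.** In Sample Size, state that the 80% power refers only to the regression F test and does not apply to the prediction objective. Drop the implication that it secures accurate prediction. In its place give the expected 95% half-width of the AUC at the test-cohort size, and the power of the model comparison, each with its assumptions and a range over dropout, prevalence and AUC. Keep enrolment as planned. Round 178.75 up to 179 or note that the difference is negligible.

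Optionally, add a performance estimate from all completers by nested cross-validation, reported alongside the held-out test result. The P < 0.05 screening and the tuning must then be repeated inside every fold. As now described, screening uses the whole training cohort before cross-validation, and out-of-fold estimates under that order would be optimistic. Replacing the held-out cohort altogether would be a larger change, since the Abstract, Figure 2 and the validation section are all built on it.

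The cost is less favourable stated figures and, for the optional part, some extra computation and text in the validation section.

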### Study Procedures

The study procedures are shown in Figure 1. Following the inclusion and exclusion criteria, eligible participants (children with BCP and PWMLs) will be entered from corrected ages of 6 to 24 months. Participants will be assessed for diagnostic criteria, differential diagnosis and comorbidities by a pediatrician or child neurologist. The participants will undergo at least 1 advance brain MRI examination according to a standardized protocol. A variety of clinical data and data pertaining to socioeconomic status will be collected. Neurobehavioral development will be assessed by experienced physiotherapists blinded to the MRI findings and related medical information (such as other examination results relevant to the content of the current assessment) at each center.

**FIGURE 1 F1:**
[figure not shown]
Flow chart of the study protocol. BCP, Bilateral Cerebral Palsy; PWML, Periventricular White Matter Lesion; MRI, Magnetic Resonance Imaging; GMFM, Gross Motor Function Measure; GMFCS, Gross Motor Function Classification System; MACS, Manual Ability Classification System; VSS, Viking Speech Scale; CBBS-DP, Communication and Symbolic Behavior Scales Developmental Profile; FCCS, Function Communication Classification System; PPTV-R, Peabody Picture Vocabulary Test-Revised; WPPSI-IV, Wechsler Preschool and Primary Scale of Intelligence.

At the age of 48–60 months, the participants will be invited back to the hospital for a follow-up assessment. Experienced speech and language therapists (SLTs) blinded to the medical history will assess each child’s communication ability using multiple classification systems and scales. The primary outcome measure for this study is the communication function classification system (CFCS) rating. Secondary outcome measures include ratings from the Functional Communication Classification System (FCCS), Viking Speech Scale (VSS), Peabody Picture Vocabulary Test-Revised (PPTV-R), verb comprehension subtest of the Wechsler Preschool and Primary Scale of Intelligence (WPPSI-IV), and CSBS-DP Infant-Toddler Checklist. The questionnaire data (CSBS-DP) will be collected by trained researchers during a telephone survey for participants who are reluctant to return to the hospital for follow-up. Other measures, such as Gross Motor Function Classification (GMFCS), Manual Ability Classification System (MACS), WPPSI-IV, and advanced brain imaging, will also be used to evaluate the development of participants during the follow-up assessment.

### Blinding

The neuroradiologists involved in lesion delineation and MRI analysis will be blinded to other clinical information and assessment findings. The child neurologists and physiotherapists conducting the neurobehavioral assessment at baseline will be blinded to the MRI findings. Follow-up assessments will be implemented once the children are old enough for preschool by SLTs blinded to the children’s clinical history, baseline assessment and MRI findings.

### Clinical Data Collection

#### Demographic Data

Basic demographic and clinical information will be collected from families and health records. The following general information will be collected: age at MRI examination, sex, body weight, height, medical history, comorbidities, epilepsy, family makeup, seizure history, and medication. In addition to the above information, prenatal factors have also been shown to be related to brain injury and affect language development outcomes. Thus, birth history variables, including delivery mode, gestational age, birth weight, head circumference, body length, and Apgar score, will also be documented.

Furthermore, a systematic review (Vaillant et al., 2020) indicated that the factors in some domains of the International Classification of Functioning, Disability and Health – Children and Youth framework are relevant for language comprehension in children with CP. According to this concept, children’s motor type, motor distribution, hand function (MACS), gross motor function (GMFCS), hearing function, visual function, speech function, socioeconomic status, parental educational level, parental occupation, and birth order will be recorded.

#### Primary Outcome Measures

The aim of the present study is to predict communication performance in children with CP at school entry. This will be assessed using the CFCS, which contains 5 levels (I-V), with level I being the best functional and level V being the least functional level. Children will be classified into one of the 5 levels based on their performance in sending and receiving information with familiar and unfamiliar communication partners. The CFCS is the most widely used system designed to classify communication function in children with CP in daily life. To increase the accuracy of the assessment, this study will establish a standardized assessment process according to a previous study (Wang and Wei, 2017). In this process, (I) SLTs will question parents regarding different aspects of the child’s daily function and simultaneously observe children’s movements during the initial contact (understanding and discovering the ways in which the child usually communicates), (II) the child’s communication with the family will be observed and recorded, and (III) SLTs will further communicate with the child through play to allow the child to fully demonstrate his or her communication skills.

While the SLTs are conducting the on-site CFCS rating, a caregiver will be asked to read the CFCS-Chinese version and conduct a retrospective assessment of the child’s communication performance in daily life. Then, the caregiver will be asked to determine his or her child’s CFCS level by taking into account the communication performance status on site. If there are 2 caregivers in the field, the ratings will be made simultaneously without discussion, and the one who spends more time with the child will be marked as the first caregiver and the other one will be marked as the second caregiver. The SLT will explain the CFCS language but will not discuss the CFCS outcome with the parents. The final CFCS levels will be determined by professionals (SLTs) in close collaboration with parents. The CFCS has good reliability with high intraclass correlation coefficients across different language versions (Hidecker et al., 2011; Vander Zwart et al., 2016; Wang and Wei, 2017; Choi et al., 2018; Mutlu et al., 2018) and has been widely used in multiple CP registries (Coleman et al., 2015; Hustad et al., 2016; Mei et al., 2016; Vander Zwart et al., 2016; Wang and Wei, 2017; Mutlu et al., 2018) as a recommended, suitable tool for evaluating everyday communication in children with CP. The CFCS-Chinese version has also shown good reliability with intraclass correlation coefficients of 0.88 between an SLT and a caregiver and of 0.86 between the first and second caregivers for children with CP (Wang and Wei, 2017).

#### Secondary Outcome Measures

The secondary outcome measures include the levels/scores of the FCCS, VSS, PPTV-R, CSBS-DP, and the vocabulary subtest of WPPSI-IV for implementing a comprehensive communication assessment of children with CP. Table 1 describes the classification systems of the CFCS, FCCS, and VSS.

(1)FCCS: The FCCS is a 5-level system, with the highest level (level V) indicating the worst performance. The FCCS classifies children’s performance in sending communicative messages and considers their observable communication performance using speech, gestures, and/or augmentative and alternative communication. The reliability and validity of the FCCS for classifying the functional communication of children with CP aged 4 to 5 years have been previously tested (Barty et al., 2016).(2)VSS: The VSS (Pennington et al., 2013) was developed to classify the speech production of children with CP. The VSS is a four-level rating scale used to classify speech intelligibility in children with CP aged 4 years and above when they are speaking to unfamiliar partners and strangers. It has substantial to almost perfect test-retest reliability (κ > 0.68) and moderate to substantial interrater reliability between pairings of professionals and/or parents (κ = 0.58–0.81) (Pennington et al., 2013).(3)PPTV-R: The PPTV-R is often used to assess the receptive vocabulary abilities of people ranging in age from 2.5 to 40 years old, and the reliability and validity of the Chinese version have been previously tested (Sang and Miao, 1990). The test is composed of 175 items, and its test-retest reliability and split-half reliability are 0.94 and 0.99, respectively. One point is recorded each time a picture is correctly matched to the given word. The raw score is obtained by summing all the correct item scores.(4)CSBS-DP: The CSBS-DP (Wetherby and Prizant, 2002) is a parent questionnaire containing 24 questions and investigates children’s expressive and receptive language skills; verb/non-verbal communication skills; and symbolic skills, such as participation in pretend play and appropriate use of objects. The total raw scores are converted to a standardized score, with mean = 100 and standard deviation (SD) = 15 among typically developing children (Wetherby and Prizant, 2002). Scores below 80 imply developmental delay of communication and referral for further language and speech assessment. The test–retest reliability of the CSBS-DP for the composite and total scores ranged from 0.79 to 0.88 (Wetherby and Prizant, 2002), and the reliability and validity of the Chinese version were previously tested (Lin et al., 2015).(5)WPPSI-IV: The Chinese version of the WPPSI (Zhang, 2009) is divided into two groups of tests: group 1 for children aged 2.5 years to 3 years and 11 months and group 2 for children aged 4 years and 0 months to 6 years and 11 months. The WPPSI-IV comprises 3 subtests (verbal comprehension, working memory and visuospatial ability) for group 1 but 5 subtests (verbal comprehension, working memory, visuospatial ability, fluid intelligence and processing speed) for group 2. The verbal comprehension test includes three subtests: similarity, comprehension, vocabulary, and a supplemental subtest—common sense. Verbal comprehension index scores have a mean = 100 and standard deviation = 15. If children with CP are unable to complete the verb comprehension subtest due to fine motor impairment, language impairment or reduced intellectual ability, a composite score will be calculated.

**TABLE 1 T1:** Descriptors for levels of the CFCS, FCCS, and VSS.

Level	CFCS	FCCS	VSS
I	Effective sender/receiver with familiar/unfamiliar partners	Effective communicator in most situations	No speech motor disorder indicated
II	Effective, but slower-paced sender and/or receiver with familiar and/or unfamiliar partners	Effective communicator in most situations but may need help	Speech motor disorder indicated but is usually understandable to unfamiliar listeners
III	Effective sender and receiver with familiar partners; not effective with unfamiliar partners	An effective communicator in some situations	Speech motor disorder indicated and is not typically understandable to unfamiliar listeners out of context
IV	Inconsistent sender and/or receiver with familiar partners; not effective with unfamiliar partners	Assistance required in most situations, especially with unfamiliar partners	No understandable speech
V	Seldom effective sender/receiver with familiar partners; not effective with unfamiliar partners	Communicates unintentionally using movements and behavior	–

*CFCS, Communication Function Classification System; FCCS, Functional Communication Classification System; VSS, Viking Speech Scale.*

